## Abstract

**Introduction:**

Esophageal cancer (EC) patients face significant challenges in health management across different disease stages, including symptom monitoring, treatment adherence, and long-term self-care. Digital health interventions, particularly mobile health (mHealth) applications, hold promise for providing personalized support and improving patient engagement. However, many existing mHealth tools for esophageal cancer lack a strong theoretical foundation and fail to fully incorporate patient-centered considerations, which may limit their long-term effectiveness. This study aims to develop and evaluate a WeChat-based mini-program that integrates Patient Journey Mapping (PJM) and the Integrated Theory of Health Behavior Change (ITHBC) to support personalized health management for esophageal cancer patients.

**Methods:**

This study will adopt a single-arm, exploratory design. Semi-structured interviews with esophageal cancer patients will first be conducted to identify their health management needs. Based on these findings, a WeChat-based mini-program will be developed and iteratively refined through Delphi expert consultation. In the evaluation phase, a mixed-method usability assessment will be performed, incorporating the mHealth App Usability Questionnaire (MAUQ), task-based performance metrics, and backend interaction analytics. To supplement these quantitative measures, brief post-test interviews will be conducted to capture user experiences and contextual factors. The primary outcome is system usability. Secondary outcomes include task completion performance, while backend interaction data will serve as process indicators of user engagement.

**Discussion:**

The findings of this study will provide insights into the user experience and system functionality of a WeChat-based mini-program designed for esophageal cancer patients. The results will inform refinements to the intervention, ensuring better alignment with patient needs and enhancing the feasibility of digital health solutions in oncology care. Furthermore, by integrating patient journey insights, this study helps establish a more patient-centered approach to mHealth design. This approach may serve as a foundation for future digital health tools supporting cancer care and long-term health management.

**Clinical trial registration:**

https://www.chictr.org.cn, Chinese Clinical Trial Registry: ChiCTR2500098611.

## Introduction

1

Esophageal cancer (EC) is an aggressive malignancy and ranks as the sixth leading cause of cancer-related mortality worldwide (1). In 2020, an estimated 604,000 new cases and 544,000 deaths were reported globally (2), with China accounting for more than half of the total burden (3, 4). Despite progress in multimodal treatment, including surgery, chemotherapy, and radiotherapy (5), the overall prognosis remains poor, with a 5-year survival rate of approximately 30% (6). The disease trajectory is often complex, characterized by a high symptom burden, post-operative complications, and significant impairments in quality of life (7–9).

Effective long-term management is therefore essential for improving prognosis and quality of life (10). Patients often face multiple health challenges throughout the disease trajectory, including dysphagia, malnutrition, fatigue, and psychological distress (11–14). Although health management needs have been recognized (15, 16), most existing interventions focus on isolated symptoms, such as pain control or nutritional issues (17–19), rather than addressing the disease trajectory comprehensively. Personalized health management interventions have been shown to significantly improve symptom control and enhance patients' quality of life (20, 21). However, conventional approaches are constrained by limited healthcare resource, suboptimal patient adherence, and poor information accessibility, making continuous and individualized support difficult to implement.

With the rapid advancement of mobile internet technologies, mobile health (mHealth) interventions have become integral to chronic disease management and cancer care (22, 23). These interventions help overcome the temporal and spatial constraints of traditional healthcare models (24), delivering personalized and accessible healthcare solutions while potentially reducing medical costs (25, 26). WeChat Mini Programs, a widely adopted and cost-effective digital platform, have been increasingly utilized in health interventions, demonstrating their potential to enhance patient self-management and improve health outcomes (27, 28).

However, despite the promising applications of mHealth tools in disease management, existing digital health interventions are primarily designed based on expert opinions and literature reviews, which may fail to fully capture patients' actual needs, leading to suboptimal user engagement and low long-term adherence (29, 30). Moreover, the lack of robust theoretical frameworks and empirical validation further limits their clinical applicability, highlighting the need for more patient-centered and evidence-based approaches.

Patient Journey Mapping (PJM) is a valuable tool for systematically identifying patients' evolving needs throughout disease progression (31, 32). Addressing the limitations of expert-driven intervention design, PJM provides a structured approach to capturing real-world patient experiences, encompassing physical symptoms, psychological distress, and social challenges (33, 34). Through methods such as in-depth interviews and patient-reported outcomes, PJM uncovers care gaps and informs service optimization (35). In EC care, where patients navigate a prolonged and complex treatment journey, PJM-based mHealth strategies offer a promising framework for developing targeted, patient-centered interventions. While PJM has been successfully incorporated into mHealth design for selected chronic and population-specific conditions (36–38), its potential in EC remains unexplored. Given the multifaceted needs of EC patients, leveraging PJM as a foundation for mHealth interventions could enhance patient engagement, improve long-term adherence, and optimize health management.

As the theoretical foundation of this study, the Integrated Theory of Health Behavior Change (ITHBC) was selected to guide the intervention development. Traditional models such as the Health Belief Model (HBM) and Transtheoretical Model have been widely used in behavior change research (39, 40); however, they tend to emphasize individual cognition or discrete stages and do not provide an integrative, process-oriented perspective for sustaining long-term behavior change. In contrast, ITHBC combines multiple theoretical perspectives and emphasizes a patient-centered, interactive, and motivational process of behavior change (41). Its core constructs include self-efficacy, emotional support, and social facilitation, which collectively promote the transition from health beliefs to actions and help maintain health-promoting behaviors (42, 43). Given its comprehensive, process-based structure, ITHBC is well-suited to inform the design of personalized, stage-based mHealth interventions for EC patients.

This study adopts the patient journey approach to systematically identify key challenges and employs ITHBC as a theoretical foundation to guide the design of a WeChat-based mini program for EC management. The primary objective is to assess the usability and user experience of the platform, examining its functionality, ease of use, and relevance to patient needs. Findings from the usability evaluation will inform iterative refinements and guide future research directions.

## Materials and analysis

2

This study adopts a single-arm, exploratory design comprising three sequential phases to guide the development and preliminary evaluation of a WeChat-based digital health platform for patients with esophageal cancer (EC). Phase 1 applies Patient Journey Mapping (PJM) to systematically assess patient needs and care experiences. Phase 2 integrates patient insights and expert recommendations into the platform's design. Phase 3 evaluates the platform's usability and acceptability to ensure alignment with patient needs. The timeline of enrolment, development, and evaluation activities is detailed in Table 1, and the study design flowchart is shown in Figure 1.

**Table 1 T1:** Study schedule for enrolment, data collection, and usability evaluation.

**Timepoint/Phase**	**Week-1 (Preparation)**	**Phase 1: Qualitative Interviews (Month 1–2)**	**Phase 2: Platform Development (Month 3–4)**	**Phase 3: Usability Testing (Month 5–7)**
Eligibility and Consent		√		√
Demographics^*^		√		√
Interview Guide Development	√			
Qualitative Interviews		√		
Delphi expert consultation			√	
Platform Development Planning	√		√	
Task-based Testing				√
mHealth App Usability Questionnaire (MAUQ) ^**^				√
Backend Data Collection				√
Post-test interviews				√

^*^Eligibility and demographics were collected separately for Phase 1 and Phase 3 participants.

^**^mHealth App Usability Questionnaire (MAUQ) was administered after participants had used the app for 1 month.

**Figure 1 F1:**
[figure not shown]
Overview of the study design and key methodological components. The figure presents the three-phase structure of the study, comprising Phase 1 (semi-structured interviews to identify patient needs), Phase 2 (mini-program development and expert refinement), and Phase 3 (mixed-method usability evaluation using quantitative metrics and post-test interviews). Key activities and expected outputs of each phase are summarized to illustrate the overall research process.

The study will conform to the principles of the Declaration of Helsinki. This study was approved by the Medical Research Ethics Committee of Suining Central Hospital (KYLLKS20250009) and is registered in Chinese Clinical Trial Registry (Registration Number: ChiCTR2500098611) before the enrollment of the first participant. In addition, this mHealth intervention will be guided by the WHO mHealth Evidence Reporting and Assessment (mERA) (44) checklist to ensure comprehensive documentation of the intervention components and implementation procedures.

### Phase 1: patient journey mapping

2.1

The first phase, Patient Journey Mapping (PJM), aims to gain in-depth insights into the experiences and challenges of EC patients. A descriptive qualitative approach will be employed, using semi-structured interviews to explore patients' self-management challenges and support needs. Findings from this phase will inform the design of core functionalities for a patient-centered digital health platform.

#### Sample/participants

2.1.1

Participants will be recruited from the thoracic surgery and oncology departments of a tertiary hospital in Sichuan Province. Eligible participants must have completed primary treatment, such as surgery, neoadjuvant therapy, and/or adjuvant therapy, and be within 3–12 months post-treatment. The inclusion criteria are as follows: (1) histopathologically confirmed diagnosis of esophageal cancer according to standard clinical diagnostic criteria (45); (2) age between 18 and 75 years; (3) adequate cognitive function and the ability to communicate effectively; (4) voluntary participation with signed informed consent. The exclusion criteria include: (1) concurrent diagnosis of other malignancies; (2) end-stage disease, defined as an expected survival of ≤ 6 weeks; (3) severe cardiovascular disease, or hepatic or renal failure; (4) history of psychiatric disorders or cognitive impairment.

#### Sample size and recruitment

2.1.2

Potential participants will be identified through follow-up outpatient clinics. Researchers will collaborate with clinic physicians to screen individuals who meet the inclusion criteria. Eligible candidates will be approached during their scheduled follow-up visits and invited to participate in a retrospective semi-structured interview.

A maximum variation sampling strategy will be employed to capture diverse perspectives, ensuring variation in sociodemographic backgrounds and treatment experiences. Based on the principle of data saturation, approximately 18 participants will be recruited. Recruitment will conclude when no new themes or concepts emerge from subsequent interviews.

#### Data collection and management

2.1.3

Semi-structured interviews will be conducted by a trained researcher. Drawing on a comprehensive literature review and expert consensus (46), a structured interview guide will be developed to explore key domains of the esophageal cancer care experience. Open-ended questions will be employed to facilitate in-depth exploration of participants' experiences. A summary of the interview domains and sample questions is provided in Table 2.

**Table 2 T2:** Overview of semi-structured interview questions about participants' health journey.

**Topic**	**Key question**
Health Issues and Symptom Management	Initial symptom characteristics; treatment-related discomfort; post-operative challenges; persistent rehabilitation issues
Psychological and Emotional Support	Emotional reactions to diagnosis; anxiety during treatment; adequacy of support systems; demand for psychological interventions
Health Information Needs and Accessibility	Information sources; treatment comprehension; rehabilitation guidance needs; barriers to reliable information; Unmet needs
Healthcare Experience and Communication	Provider communication quality; hospital process efficiency; communication barriers; service improvement suggestions
Demand for Health Management Tools	Mini-program adoption willingness; functional requirements; content format preferences; caregiver assistance needs

Prior to the interview, the researcher will establish rapport with participants, introduce the study objectives, and obtain written informed consent. Interviews will be conducted either in a private hospital setting or via secure, encrypted online platforms, depending on participants' preferences. Each session will last approximately 40–50 min. With participants' consent, all dialogues will be audio-recorded, and non-verbal cues will be documented.

Transcriptions will be generated verbatim and anonymized to protect confidentiality. Each dataset will be assigned a unique identifier, with all personally identifiable information removed. Data will be securely stored with restricted access, available only to authorized research team members.

#### Qualitative data analysis and patient journey mapping

2.1.4

Qualitative data will be analyzed using conventional content analysis. Audio recordings will be transcribed verbatim within 24 h of each interview to maintain contextual accuracy. Two independent researchers will code the transcripts using NVivo 12 Plus software, with discrepancies resolved through discussion or third-party review.

A patient journey map will be constructed to visually represent patients' evolving needs across distinct treatment phases. The initial framework will be established based on a literature review and clinical expertise. Interview data will be iteratively analyzed and incorporated to refine the framework, ensuring a comprehensive representation of patient experiences (47). To enhance the credibility and patient-centeredness, patient representatives will be invited to review the journey map and provide feedback (48).

### Phase 2: development of the WeChat mini-program

2.2

This phase aims to design and develop a WeChat-based mini-program to support the health management of EC patients, based on insights from Phase 1 and refined through input from clinical experts. The platform will be developed through an iterative process incorporating feedback from patients, clinicians, and digital health experts, ensuring patient-centered design and continuous alignment with evolving clinical practices and evidence.

#### Establishment of a multidisciplinary research team

2.2.1

(1) Team composition: a multidisciplinary research team is established, including senior nurses, attending physicians, nursing informatics specialists, dietitians, psychologists, software engineers, and graduate nursing students. This collaborative approach fosters effective interdisciplinary integration, enhancing both the scientific rigor and practical applicability of the mini-program.(2) Team responsibilities: the team is responsible for transforming qualitative research findings into functional specifications, verifying content for medical accuracy and scientific validity, and developing the program within the WeChat ecosystem. Iterative testing is conducted to refine and optimize the mini-program.(3) Quality control: biweekly meetings are held to monitor development progress. A structured review process ensures compliance with quality standards, and any issues encountered are promptly addressed to maintain consistency and reliability.

#### App functionality modules

2.2.2

The mini-program's functional modules are initially defined through multidisciplinary team discussions, a review of existing literature, and alignment with the ITHBC framework (Figure 2). To provide a preliminary overview of the planned intervention components, a draft list of core functional modules is presented in Table 3. These modules are subject to further refinement based on findings from qualitative research and expert panel consultation, to ensure responsiveness to patient needs. For example, if psychological support is found to be of lower relative priority based on patient feedback, the corresponding module may be adjusted or integrated into broader support features. In addition, expert consensus will also evaluate the feasibility and prioritization of each module, strengthening the intervention's scientific foundation and practical value.

**Figure 2 F2:**
[figure not shown]
Conceptual framework of the Integrated Theory of Health Behavior Change (ITHBC). The figure depicts the three core constructs of the ITHBC—knowledge and beliefs, self-regulation skills and abilities, and social facilitation—and their interrelationships. These constructs form the theoretical foundation for this study and provide a conceptual basis for understanding health behavior change among esophageal cancer patients. The framework informs the overall direction of intervention development without depicting the specific functional modules of the mini-program.

**Table 3 T3:** Preliminary functional components of the digital health intervention based on ITHBC.

**Functional module**	**Tentative description**	**Corresponding theoretical construct (ITHBC)**
Personal Center (“Me”)	User profile, disease stage information, feedback, privacy settings, data archive	Self-monitoring, Engagement
Symptom Tracker	Daily symptom logging, warning alerts, and visualized reports	Self-regulation, Self-monitoring
Knowledge Hub	Provides curated Q&A-style health education tailored to different disease stages	Knowledge & Belief
Health Reminders	Covers medication, appointments, and physical activity reminders	Self-regulation Skills
Emotional Support	Delivers coping strategies or access to psychological resources	Social Facilitation, Emotional Support
Peer and Professional Support	Facilitates peer interaction, expert Q&A, and experience sharing	Social Facilitation, Belief Support
Diet and Nutrition	Offers adaptive dietary guidance and interactive nutrition tools	Knowledge & Belief, Self-regulation Skills

### Phase 3: evaluation

2.3

Upon completion of development, the mini-program will undergo a mixed-method usability evaluation. Quantitative measures will draw on the mHealth App Usability Questionnaire (MAUQ), demographic and eHealth literacy (eHEALS) questionnaires, backend interaction analytics, and structured task-based performance metrics. To complement these data, brief post-test interviews will be conducted to explore users' experiences, perceived barriers, and improvement suggestions. Insights derived from integrating performance metrics with user narratives will guide iterative refinements and ensure that the program meets the needs of patients, caregivers, and healthcare professionals. All usability testing procedures and outcomes will be documented in accordance with ISO/IEC 25062 (49) (Common Industry Format for Usability Test Reports) for standardized and comprehensive reporting.

#### Sample/participants

2.3.1

A convenience sampling method with consecutive recruitment will be used to enroll three participant groups: esophageal cancer patients, their primary caregivers, and healthcare professionals. The expected sample size for each group will be described in detail in subsequent sections. Eligibility criteria include age ≥18 years, provision of written informed consent, and basic smartphone literacy.

All participants will continue to receive routine clinical care and follow-up as prescribed by their healthcare providers. The use of the digital health intervention will not interfere with any ongoing medical treatment or supportive care. No specific concomitant interventions are restricted or prohibited during the study.

**(1) Patients**

Inclusion criteria: histologically confirmed esophageal cancer at the diagnostic, treatment, or recovery phase. ability to independently perform basic smartphone operations.

Exclusion criteria: severe cognitive impairment (Mini-Mental State Examination [MMSE] score <24) or psychiatric disorders. coexisting advanced malignancies or terminal diseases with an expected survival of <6 months. inability to understand Chinese or complete the testing procedures.

**(2) Primary caregivers**

Inclusion criteria: directly providing care for the patient for ≥ 20 h per week for ≥1 month. no severe visual or hearing impairments.

Exclusion criteria: presence of severe chronic illnesses. conflicts of interest with the patient (e.g., legal disputes).

**(3) Healthcare professionals**

Inclusion criteria: oncologists, thoracic surgeons, or nurses with ≥2 years of clinical experience in EC care. Having managed ≥ 5 EC patients in the past 6 months.

Exclusion criteria: involvement in the development of similar digital tools within the past year. Inability to complete the full usability testing process.

#### Sample size and recruitment

2.3.2

A stratified sampling strategy will be employed to ensure representation of key user groups and disease phases. Evidence from usability research indicates that approximately 10–12 participants are sufficient to identify the majority of usability issues (50, 51). To obtain sufficiently stable descriptive metrics, the planned sample sizes are set as follows: 12–18 patients across major disease phases, 8–12 primary caregivers, and 8–12 healthcare providers. Allowing for an anticipated 20% attrition rate, the target sample size is 34–40 participants. Participants will be recruited through ward posters, outpatient clinic flyers, and referrals from healthcare staff. Eligible individuals will be identified, provided with detailed study information, and enrolled upon obtaining written informed consent. Qualitative feedback will be collected from the same participants through brief post-test interviews. As these interviews are intended to inform formative usability evaluation and identify improvement needs, no formal sample size calculation is required for this component.

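### The Phase 3 target of 34–40 does not follow from the group sizes and 20% attrition: its upper end is below the group total before any attrition

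*Protocol article*

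**What the plan says.** The Phase 3 sample size is set in one place, section 2.3.2 (Sample size and recruitment) of the protocol article. Section 2.3.1 defers the group sizes to later text, and no other section gives them or the total.

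- **Group sizes:** "12–18 patients across major disease phases, 8–12 primary caregivers, and 8–12 healthcare providers". Their stated purpose is stable descriptive results.
- **Total:** "Allowing for an anticipated 20% attrition rate, the target sample size is 34–40 participants".
- **Background:** usability research is cited to the effect that "approximately 10–12 participants are sufficient to identify the majority of usability issues".

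The section does not give the sum of the groups, the formula used for attrition, or how 40 was reached. It also does not say whether the group sizes count people enrolled or people who complete.

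**The concern.** The two sentences stand next to each other and cannot both be followed as written. The second presents the total as the result of adding an allowance for attrition to the first. Such an allowance cannot reduce a number, but the top of the range goes down.

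What is at stake is practical. A recruiting team cannot tell whether to stop at 40 or to go on filling the group ranges, and a later reader cannot judge whether recruitment reached its goal. Completers are the number that matters. Section 2.3.3 collects the usability questionnaire (the primary outcome) only at one month, and section 2.3.4 places the task tests at the end of the trial. Anyone lost before then contributes to neither.

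**Working it through.** **Inputs, all from section 2.3.2**

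- Patients 12–18, caregivers 8–12, healthcare providers 8–12.
- Attrition d = 0.20.
- Stated total 34–40.

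**Step 1. Sum of the groups**

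- Lower: 12 + 8 + 8 = 28.
- Upper: 18 + 12 + 12 = 42.

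**Step 2. Try to reproduce 34–40**

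| Reading | Lower | Upper |
|---|---|---|
| Stated | 34 | 40 |
| n/(1 − d), groups are completers | 28/0.8 = 35 | 42/0.8 = 52.5, so 53 |
| n × (1 + d) | 28 × 1.2 = 33.6, so 34 | 42 × 1.2 = 50.4, so 51 |
| n/(1 − d), patients only | 15 + 16 = 31 | 23 + 24 = 47 |
| 10–12 in each of three groups, × 1.2 | 30 × 1.2 = 36 | 36 × 1.2 = 43.2 |
| 10–12 in each of three groups, /0.8 | 30/0.8 = 37.5 | 36/0.8 = 45 |

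No row gives 34–40. The lower end appears under n × 1.2. The upper end appears under none. Midpoints do not help: 15 + 10 + 10 = 35, and 35 × 1.2 = 42, while 35/0.8 = 43.75.

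**Step 3. The formula that delivers the planned completers**

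If a fraction d is lost, enrolling N leaves N(1 − d), so N = n/(1 − d). Rounded up by group:

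- Patients: 12/0.8 = 15 to 18/0.8 = 22.5, so 15–23.
- Caregivers and providers, each: 8/0.8 = 10 to 12/0.8 = 15.
- Total: 35–53.

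**Step 4. What the stated target yields**

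- 34 enrolled: 34 × 0.8 = 27.2 completers, against a minimum of 28.
- 40 enrolled: 40 × 0.8 = 32 completers. This is 4 above the minimum of 28 and 10 below the maximum of 42 (10/42 = 24%).

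**Step 5. Which group sizes fit within 40**

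- All minima: 15 + 10 + 10 = 35. Fits.
- One smaller group at its maximum, the others at their minima: 15 + 15 + 10 = 40. Fits, leaving 12, 12 and 8.
- Patients at their maximum, the others at their minima: 23 + 10 + 10 = 43. Does not fit.
- All maxima: 53. Does not fit.

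**Step 6. Effect on precision**

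Section 2.3.5 reports the primary outcome as a mean with SD and 95% confidence interval. Assuming one pooled mean, which the article does not state, the half-width in SD units is t/√n: 2.020/√42 = 0.31 with 42 completers and 2.040/√32 = 0.36 with 32.

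**The case against.** The strongest reply is that three flexible ranges need not all reach their maxima together. A total narrower than their sum is then not impossible in itself, and 34–40 does lie inside 28–42. On that view the group sizes may be enrolment numbers, and 40 is simply a cap. This stands in part: the article does not say that the ranges are completers, so 35–53 is the consequence of one reading and not a proven intention. It does not rescue the sentence, which offers 34–40 as the result of allowing for attrition. If the ranges are enrolment numbers, nothing has been allowed for, and the expected completers are 28 × 0.8 = 22.4 to 42 × 0.8 = 33.6.

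The second reply is that the lower end is sound, and it largely is. A gap of 34 against 35 is one person, and any enrolment from 35 to 40 is expected to cover every group minimum.

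The third is that the design is single-arm and exploratory, with no power calculation to undermine. That also stands and limits the weight of the point.

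A reader might further infer that a floor of 8 caregivers and 8 providers breaks the protocol's own standard of 10–12. The text does not support this. Section 2.3.2 cites 10–12 as enough to find most usability problems. It does not apply the figure to each group or make it a minimum, and it gives the group sizes a different purpose.

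**Conclusion.** The stated target is wrong as written. The error that matters is the upper end: 40 is 2 below the group total of 42 before attrition, and 13 below the 53 needed if all maxima are to be met by completers. The lower end is off by one at most.

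The size is modest. With 20% attrition, 40 enrolled covers the planned minima but not the maxima together, nor the patient maximum alongside the other two minima. It would be tempting to conclude that the study is too small or that its results are compromised. The document does not support that: no power is claimed, and the loss of precision between 42 and 32 completers is small.

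The figures 35–53 and 32 rest on two assumptions: that the group sizes mean completers, and that attrition is 20% in every group. The conflict between 40 and 42 rests on neither. This is a should-fix point.

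**What to change.** Restate the figures in section 2.3.2 so that they agree, and say whether the group sizes count people enrolled or completers. There are two ways to do this without enrolling beyond the present cap of 40 where it is kept.

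1. **Keep the cap at 40 and treat the group sizes as completers.** State 35–40 enrolled for 28–32 expected completers (35 × 0.8 = 28; 40 × 0.8 = 32). Narrow the three group ranges so that they sum to 28–32. The cost is less favourable upper group sizes: together the maxima fall from 42 to 32. No one is enrolled beyond the present cap.

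2. **State that the group ranges are enrolment numbers.** Give the expected completers as about 22–34 (22.4–33.6) and reword the attrition clause, since the total is then not an inflated one. If 34–40 is kept as a narrower total, say so and give about 27–32 completers. The cost is that the expected completers at the group minima fall from 28 to about 22.

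Keeping all the present ranges as completer numbers would mean a target of 35–53, up to 13 more people than the cap, at one centre and within the months 5–7 that Table 1 allots to usability testing.

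The Data Availability statement says that no data have been collected, so either correction can still be made in advance. The first changes three ranges and one total. The second changes mainly one sentence.
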